#### Microbiome analysis

The raw 16S rRNA gene data will be processed to generate amplicon sequence variants (ASVs) using DADA2 program [25]. Taxonomies will be assigned using Silva [26] as the reference database. Alpha diversity (such as Observed ASVs, Chao1, Shannon, Simpson, etc.) and beta diversity measures will be analyzed using QIIME2 [27] and the Wilcoxon and Kruskal–Wallis tests will be used for statistical testing of two and multi-group comparisons, respectively. Principal coordinate analysis will be used to interrogate the robustness of group-wise clustering, and Adonis test will be used to estimate statistical significance of group-wise beta diversity [27]. Generalized linear model (GLM) will be performed to evaluate the influence factors that may affect the gut microbiota of patients, such as gender, body mass index, TB severity, age, morbidities and so on [28]. Then using GLM to estimate the dynamic changes of microbiota composition with the control of selected confounders [29]. Differential abundance analysis of ASVs will be carried out using STAMP [30] and *p*-values will be adjusted for multiple testing (FDR-adjusted Wald Test). Correlations between clinical parameters and bacterial genera will be calculated using canonical correspondence analysis or redundancy analysis [31]. Random forests approach will be performed to find the most important species as marker taxa correlating with unfavorable treatment outcomes. The data will be analyzed using the QIIME2 pipeline and R [32]. A *p*-value or q-value ≤0.05 will be considered as statistically significant.

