### Sample size

Because of the absence of prior data on the study aims of the microbiota in a cohort study design of this topic, a pragmatic approach is chosen to determine the sample size. Based on the previous collaboration with the study sites, each site should enroll 50 eligible TB patients every year so that a patient cohort of 300 cases is expected within 2 years. Referred to the treatment failure rate (10%) in China [1], 30 patients in the conducted cohort are estimated to have unfavorable treatment outcomes. The sample size of microbiota study is usually selected empirically, a wide range of study settings indicates that 30 patients each group would likely be sufficient to assess phenotypic heterogeneity at the molecular level [21, 22].

Healthy controls will be equally recruited from the population taking routine health check-up in Sichuan and Shanghai with a total amount of 60. By assuming the rates of intestinal flora dysbiosis are 20% in TB patients [11] and 5% [23] in healthy controls [23], the sample size of 200 TB patients and 60 healthy controls has over 85% power to detect a significant difference in the composition of gut microbiota at the 5% significance level.

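### Adonis is planned without a dispersion check for groups stated as 60 vs 200, so unequal spread can produce a false composition shift or hide a real one, depending on which group is more variable

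*Protocol article*

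**What the plan says.** In the protocol article, under Statistical analysis, Microbiome analysis, the test tied to differences between groups in beta diversity is Adonis: "Adonis test will be used to estimate statistical significance of group-wise beta diversity". Beside it stands an ordination: "Principal coordinate analysis will be used to interrogate the robustness of group-wise clustering". The preceding sentence covers alpha and beta diversity together: "beta diversity measures will be analyzed using QIIME2 [27] and the Wilcoxon and Kruskal–Wallis tests will be used for statistical testing of two and multi-group". The decision rule is "A *p*-value or q-value ≤0.05 will be considered as statistically significant". No test of within-group dispersion is named.

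The group sizes come from Sample size:

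- **Patients against healthy controls:** power is claimed for "the sample size of 200 TB patients and 60 healthy controls".
- **Outcome comparison:** "a patient cohort of 300 cases is expected within 2 years", of whom "30 patients in the conducted cohort are estimated to have unfavorable treatment outcomes". The same paragraph argues that "30 patients each group would likely be sufficient to assess phenotypic heterogeneity at the molecular level".

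Secondary objectives and Study design make the outcome comparison a nested case-control study. Neither gives the number of controls per case.

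**The concern.** Adonis (permutational ANOVA on distances) permutes group labels. Its null hypothesis is that the groups have the same distribution, not merely the same centre. With equal group sizes it is largely insensitive to unequal spread. With unequal sizes it is not: it rejects too often if the smaller group is the more variable one, and too rarely if the larger group is.

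A principal coordinate plot displays the points but does not test spread, so it does not settle which of the two has been found. At stake are two secondary aims: how patients at baseline differ from healthy controls, and how gut microbiota relates to adverse effects and treatment outcome. In both, a reader will want to know whether the typical composition differs or only the variability between people.

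**Working it through.** **1. The plan's own figures.** Ten percent of 300 is 30, as stated. For dysbiosis of 20% against 5% in 200 and 60 people, with a two-sided 5% level (sidedness assumed) and the pooled variance under the null:

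- pooled proportion = (200 × 0.20 + 60 × 0.05)/260 = 43/260 = 0.1654
- SE under the null = √[0.1654 × 0.8346 × (1/200 + 1/60)] = 0.0547
- SE under the alternative = √[0.16/200 + 0.0475/60] = 0.0399
- power = Φ[(0.15 − 1.96 × 0.0547)/0.0399] = Φ(1.07) = 85.8%

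This reproduces the claim of over 85%. It concerns two proportions, so it says nothing about how Adonis behaves, and nothing below changes it.

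**2. Why group size matters.** Let V₁ and V₂ be the mean squared distances to the centroid in groups of n₁ and n₂, with N = n₁ + n₂ and identical centroids. The two parts of the Adonis pseudo-F then have expectations

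- between groups: (n₂V₁ + n₁V₂)/N
- within groups: [(n₁ − 1)V₁ + (n₂ − 1)V₂]/(N − 2)

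With n₁ = n₂ both equal (V₁ + V₂)/2, so unequal spread does not move their ratio from 1. With n₁ = 60 controls, n₂ = 200 patients and V₂ = 1:

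| Controls' SD ÷ patients' SD (assumed) | V₁ | Between | Within | Ratio |
|---|---|---|---|---|
| 1.5 | 2.25 | 510/260 = 1.96 | 331.75/258 = 1.29 | 1.53 |
| 1.25 | 1.5625 | 372.5/260 = 1.43 | 291.19/258 = 1.13 | 1.27 |
| 1 | 1 | 1 | 1 | 1 |
| 0.8 | 0.64 | 188/260 = 0.72 | 236.76/258 = 0.92 | 0.79 |
| 0.67 | 0.444 | 148.9/260 = 0.57 | 225.2/258 = 0.87 | 0.66 |

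Permuting the labels mixes the two spreads, so the reference distribution stays near 1 while the observed statistic moves up or down.

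**3. Rejection rates at 60 vs 200**, identical centroids, nominal 5%, Euclidean distance. The article names no distance metric and no dispersion figure, so data structure and SD ratios are assumptions.

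| Simulated data | 1 | 1.25 | 1.5 | 0.8 | 0.67 |
|---|---|---|---|---|---|
| Normal, 30 dimensions, variance 1/k in dimension k (2,000 data sets, 499 permutations) | 4% | 12% | 24% | 1.6% | not run |
| Normal, 20 dimensions of equal variance (2,000 data sets, 199 permutations) | 4.8% | 19.9% | 40.9% | 0.5% | 0.05% |
| Dirichlet compositions, 60 taxa (600 data sets, 199 permutations) | 6% | 14% | 26% | 0.7% | not run |

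A further run set Adonis beside a Welch-type distance test, which divides the squared distance between centroids by V₁/n₁ + V₂/n₂. Under equal centroids the expected squared distance is exactly V₁/n₁ + V₂/n₂, so this ratio is not moved by unequal spread. Adonis gave 12% and 26% at ratios 1.25 and 1.5, and 1% and 0.2% at 0.8 and 0.67. The Welch-type test stayed at 4% to 6%. Repeating this with the variance-1/k data agreed to within 1.5 percentage points.

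**4. The outcome comparison.** The control ratio is not stated, so it has to be varied. In the Dirichlet setting, with the 30 cases more variable by 1.25 / 1.5 times:

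- 30 vs 30: 4% to 6% at both ratios
- 30 vs 60: 11% / 17%
- 30 vs 120: 16% / 35%

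In the equal-variance normal setting, 30 vs 30 gave 4.7% to 5.4% at every ratio, in either direction.

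**The case against.** The strongest reply is that this is an omission from a condensed article: Adonis is a standard test, and a dispersion check is the sort of detail that a full protocol or analysis plan may hold. That is fair as far as the missing check goes. What stands is that the article itself fixes the test, the level and the 60 vs 200 sizes, and the test applied as written to those sizes does not separate location from spread.

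Four stronger readings are tempting and are not supported:

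- **That Adonis is the only test of beta diversity.** The preceding sentence can be read as applying the Wilcoxon and Kruskal–Wallis tests to beta diversity too. Neither is offered as a dispersion check, and pairwise distances are not independent observations, so they do not remove the problem.
- **That unequal spread would produce a false finding.** This depends on direction. If patients vary more than healthy people, the larger group is the more variable one and Adonis is conservative. The risk is then a missed shift. Even in the liberal direction, most simulated data sets at 60 vs 200 did not reject.
- **That the outcome comparison is 30 vs 270.** The 270 comes only from subtracting 30 from 300. The article plans a nested case-control study and speaks of 30 per group. At 1:1 the difficulty disappears.
- **That the primary objective is affected.** It concerns change during treatment in the same patients, which is not a contrast of groups of very unequal size by design.

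It can also be said that greater spread is itself a difference in beta diversity, and that the article never promises to report a significant Adonis result as a shift in centre. That is correct. It is a reason to report dispersion separately, so that the reader can tell which of the two was found. The planned models, differential abundance analysis and constrained ordination also bear on composition, so a conclusion need not rest on Adonis alone.

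**Conclusion.** The point holds in a limited, two-sided form. For the 60 vs 200 comparison, Adonis without a dispersion check has a false-positive rate of about 12% to 26% if controls are 1.25 to 1.5 times as variable as patients, and about 1% or less if they are 0.8 to 0.67 times as variable. The direction follows from the algebra and appeared in every setting. The size depends on the assumed SD ratios and data structure, and equal variance in all dimensions gives 20% to 41% in the liberal direction.

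The outcome comparison is exposed only if the nested study uses clearly more controls than cases. The reach is the secondary between-group comparisons. No sample-size or power figure changes.

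**What to change.** Report a dispersion test (PERMDISP/betadisper) beside every between-group Adonis test. Where group sizes are unequal and spread differs, base any claim of a composition shift on a Welch-type distance test or on repeated size-balanced subsampling, and otherwise describe the result as a difference in variability. State the number of controls per case in the nested study, since a 1:1 design removes the problem for that comparison.

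The cost is a few lines of R, with no new data and no change in sample size. The downside is a little extra analysis, and some results will be reported as differences in variability instead of composition.

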**Methods:**

The study is a multicenter, observational prospective cohort study. Three study sites are purposively selected in the western (Sichuan Province) and eastern (Jiangsu Province and Shanghai) parts of China. Three-hundred patients with bacteriologically confirmed pulmonary TB are enrolled. All eligible patients should be investigated using structured questionnaires before treatment initiation; and be followed up during the treatment at Day-14, Month-2, Month-5, the end of treatment and the sixth month after ending therapy. Stool samples are to be collected at each visit, consisting of six stool samples from each patient. Additionally, 60 healthy volunteers from Sichuan province and Shanghai city will be recruited as healthy controls to form the baseline of patient gut microbiota in the Chinese population. The dynamic changes of gut microbiota in terms of alpha diversity, beta diversity, taxonomic composition are to be illustrated individually from the time at diagnosis until the sixth month after therapy is completed. Furthermore, the diversity and component of gut microbiota will be compared between the groups with and without unfavorable treatment outcome in terms of adverse effect and treatment failure.

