## Background

Tuberculosis (TB), caused by *Mycobacterium tuberculosis* (*M. tb*), has plagued humans for thousands of years and remains a major public health problem. Estimated by the World Health Organization (WHO), there were 10 million TB cases and 1.6 million TB deaths worldwide in 2017 [1]. Among them, 890,000 new TB cases (8.9%) were infected in China, with a mortality rate of 26/100,000 [1]. TB is a curable disease, and the modern TB control program recommends the strategy of directly observed treatment – short-course therapy, which is a six-month standardized treatment using first-line anti-TB drugs (FLDs) including Isoniazid (INH), Rifampicin (RFP), Pyrazinamide (PZA), and Ethambutol (EMB). This potent standardized drug regimen has contributed to an up to 90% cure rate in TB patients during the last three decades. However, the high rate of recurrence and retreatment among TB patients, the ubiquity of severe gastrointestinal adverse reactions [1, 2], and the increasing epidemic of multidrug-resistant tuberculosis (MDR-TB) all suggest that the effectiveness of anti-TB treatment in China has yet to be addressed.

Therefore, introducing new knowledge and clinical strategies to improve the therapeutic effect and clinical prognostics in Chinese TB patients is of great significance. The recent research advances in gut microbiome have shown that these bacteria are not only actively involved in the absorption of food and drugs but also produce bioactive compounds influencing the immune and hormone systems, which is essential to maintain vital functions of the healthy host [3]. Generally, the human gut microbiota shows a large degree of interpersonal diversity [4], and its composition is also affected by many factors such as geography, diet, season, lifestyle, disease state, and in particular, the use of antibiotics [3, 5].

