## Methods/design

### Objectives

#### Primary objective

The primary objective of this study is to explore the effects of continuous administration of FLDs on the gut microbiota by analyzing its alterations on diversity and taxonomic composition in pulmonary TB patients in China.

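### The model named for change over time, a generalized linear model with no stated patient effect, does not fit six samples per patient and overstates the standard error of visit effects

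*Protocol article*

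**What the plan says.** The primary objective is "to explore the effects of continuous administration of FLDs on the gut microbiota by analyzing its alterations on diversity and taxonomic composition". The data for it are longitudinal: the abstract describes a collection "consisting of six stool samples from each patient", and says that changes in diversity and composition "are to be illustrated individually from the time at diagnosis until the sixth month after therapy is completed". Study procedures and Table 2 give the same six time points, from Day-0 to six months after therapy. Under Sample size, "a patient cohort of 300 cases is expected within 2 years", so complete collection would give 300 × 6 = 1,800 samples.

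Microbiome analysis assigns one model to the time course: "Then using GLM to estimate the dynamic changes of microbiota composition with the control of selected confounders". The same section and the abbreviation list both expand GLM as generalized linear model. For alpha and beta diversity, the Wilcoxon and Kruskal–Wallis "tests will be used for statistical testing of two and multi-group comparisons, respectively", and Adonis is used for group-wise beta diversity. The article mentions no random effect, GEE, robust standard error, paired or Friedman test, or permutation restricted within patient.

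**The concern.** A generalized linear model as named assumes independent observations. Six samples from one person are not independent, and the Background gives the reason: "the human gut microbiota shows a large degree of interpersonal diversity". Stable differences between people are what make samples from the same person alike.

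Ignoring this has opposite effects on two kinds of question:

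- **Visit effects (the primary question).** Each patient is their own comparator, so differences between people should cancel. A model without a patient term leaves them in the error. Standard errors are too large, and a real change can be reported as no change.
- **Patient-level factors (sex, severity, outcome), if all visits are pooled.** One patient counts as up to six. Standard errors are too small and false associations appear. Adjusting for the false discovery rate does not repair p-values that are invalid to begin with.

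**Working it through.** **1. The plan's own figure.** The only stated power, over 85%, compares 200 patients with 60 controls at 20% and 5% dysbiosis. Pooled proportion = (40 + 3)/260 = 0.1654. Standard error under the null = sqrt(0.1654 × 0.8346 × (1/200 + 1/60)) = 0.0547; under the alternative = sqrt(0.16/200 + 0.0475/60) = 0.0399. Power = Φ((0.15 − 1.96 × 0.0547)/0.0399) = Φ(1.07) = 85.8%. The figure reproduces. It is a comparison with one sample per person, so this point does not affect it. No power is given for change within patients.

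**2. Inputs for the time course.** From the article: 300 patients, 6 samples each, 5% level (taken as two-sided), and 30 expected unfavorable outcomes. Assumed: ICC 0.3, 0.5 and 0.7 (the correlation remaining after covariates), equal correlation between all visits, complete samples, normal data with SD 1.

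**3. Standard error of a contrast between two visits.** Ignoring the patient: sqrt(2/300) = 0.0816. Correct: sqrt(2(1 − ICC)/300). The ratio is 1/sqrt(1 − ICC).

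| ICC | Correct SE | SE ignoring patient | Ratio |
|---|---|---|---|
| 0.3 | 0.0683 | 0.0816 | 1.20 |
| 0.5 | 0.0577 | 0.0816 | 1.41 |
| 0.7 | 0.0447 | 0.0816 | 1.83 |

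**4. False-positive rate for the visit effect.** In 1,000 simulated trials with no change, a linear model F test that ignores the patient rejects in 1.0%, 0.1% and 0.0% of trials (ICC 0.3, 0.5, 0.7). A repeated-measures F test holds 4.5 to 4.9%.

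**5. Power for the visit effect.** The assumed shift is present at the four visits from Day-14 to end of therapy and half recovered at the last. Kruskal–Wallis across visits stands in for any test that ignores the patient. At 0.2 SD the linear model that ignores the patient was also run: 66 / 62 / 56%.

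| Shift | Patient ignored, ICC 0.3 / 0.5 / 0.7 | Repeated measures |
|---|---|---|
| 0.15 SD | 27 / 19 / 9% | 55 / 74 / 94% |
| 0.20 SD | 62 / 59 / 52% | 88 / 96 / 99.9% |
| 0.25 SD | 88 / 92 / 93% | not run; loss at most 12 / 8 / 7 points |
| 0.30 SD | 98 / 98 / 100% | not run; loss at most 2 points |

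(The 0.20 SD row used 1,000 replicates, the other rows 600. The maximum losses are 100% minus the power shown.)

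**6. Conditional check: patient-level factor with visits pooled.** Suppose 30 patients are compared with 270 using all six samples as independent (180 against 1,620). The design effect is 1 + 5 × ICC = 2.5, 3.5, 4.5. The true error rate is 2(1 − Φ(1.96/sqrt(design effect))) = 21.5%, 29.5%, 35.6%. Simulation gives 21%, 29%, 35%.

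**The case against.** **The article is condensed.** A patient term, a GEE working correlation or permutation strata could stand in a fuller plan that is not shown. This has weight: the accurate statement is that no patient effect is stated, not that none will be used. It does not remove the point, because the article does not leave the longitudinal model open. It names one, and as named that model does not suit the design.

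**The other tests.** A reader might infer that Wilcoxon, Kruskal–Wallis and Adonis are also misapplied. The article does not support that. It ties them to group comparisons, and the groups it describes are patients at baseline against healthy controls, baseline strata, and patients with and without unfavorable outcomes. With one sample per person these tests are valid. Wilcoxon, unqualified, can also mean the signed-rank test. Only the GLM sentence is tied to change over time.

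**False associations.** A reader might also infer that the plan will produce false-positive rates near 30%. That needs visits to be pooled as if independent, which no section says. The outcome comparison is described as a nested case-control study, without saying which samples enter.

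**Underpowering.** Calling the primary analysis badly underpowered would rest on one assumed shift. Step 5 shows the loss running from severe to negligible. For visit effects the error is also conservative, and the aim is exploratory. These limits stand. They bound the consequence but do not make the named model suitable.

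**Conclusion.** The point holds for the model of change over time. Applied as named, it overstates the standard error of visit effects by about 1.2 to 1.8 times (ICC 0.3 to 0.7). Tests of change are then conservative, with confidence intervals about 20 to 83% too wide. How much power is lost depends on the true shift, for which the article gives no value.

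The anti-conservative error of roughly 20 to 35% is conditional on pooling visits for patient-level factors. It is a reason to exclude that use in the text, not a finding that the plan intends it.

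The ICC values, the shifts and the equal-correlation normal model are assumptions. The direction of both errors holds for any positive ICC under that model. Adonis was not simulated; for it the argument is about exchangeability of samples only.

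**What to change.** - Replace the GLM for change over time by a mixed model or GEE with patient as the cluster and visit as a factor, adjusted for the selected confounders.
- For any unadjusted visit contrast use the signed-rank test, or Friedman across visits. In its standard form Friedman needs complete cases, so patients missing a visit drop out; the mixed model should therefore lead.
- Where Adonis tests visit effects, restrict permutations within patient.
- Analyse patient-level factors one visit at a time, or with the patient as the unit of permutation or clustering.
- Keep Wilcoxon, Kruskal–Wallis and unrestricted Adonis for comparisons with one sample per person, and say so.

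A log-ratio transform for taxa and a fixed covariate list are optional. The cost is wording and a little more analysis work in R, which is already planned; no new data are needed. If a mixed model or GEE was always intended, one sentence saying so settles the main point.

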#### Secondary objectives

To describe the baseline features of gut microbiota before anti-TB treatment among TB patients with different age, gender, health status, disease comorbidity in different regions of China.To compare the characteristics of gut microbiota in terms of diversity and taxonomic composition between TB patients at baseline and healthy controls.To describe the incidence of gut microbiota dysbiosis during anti-TB treatment and its association with adverse effects and unfavorable treatment outcomes in pulmonary TB patients through a case-control study nested in the conducted cohort.To identify the potential microbial markers of unfavorable treatment outcomes.To observe the long-term effect of TB treatment on intestinal microbiota after therapy is completed.

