### Study design

This study is an ongoing multicenter, population-based prospective cohort study conducted in three TB designated hospitals in Eastern and Western China. The study aims to include 300–400 bacteriologically confirmed pulmonary TB patients. Baseline information, including demographics, socioeconomic status, laboratory tests, and disease profiles, as well as sputum and stool samples will be collected from the enrolled patients immediately after TB diagnosis. The patient cohort will be built and followed up during the first-line anti-TB treatment at Day-14, Month-2, Month-5, last day of treatment, and the sixth month after treatment. Information regarding adverse effects, disease progress, and laboratory results will be collected at each visit. Stool samples will be sent to the laboratory for 16S ribosomal ribonucleic acid (rRNA) gene sequencing to identify the alterations in gut microbiota. A comparison of gut microbiota will be performed between newly diagnosed TB patients and healthy controls to reflect the difference in baseline features. After treatment completion, a nested case-control study will be performed between patients with treatment success or failure and patients with or without adverse effects to screen the potential biomarkers from the gut microbiota indicative of therapeutic effect.

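### Marker taxa are chosen by random-forest importance rank alone, so the stated rule names markers even when no taxon relates to outcome

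*Protocol article*

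**What the plan says.** One of the secondary objectives is "To identify the potential microbial markers of unfavorable treatment outcomes". Under Study design, the nested case-control comparison after treatment is meant "to screen the potential biomarkers from the gut microbiota indicative of therapeutic effect".

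The method comes under Statistical analysis, Microbiome analysis: "Random forests approach will be performed to find the most important species as marker taxa correlating with unfavorable treatment outcomes". That sentence is all the article says about how a taxon becomes a marker.

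Two other statements in that section could bear on it. The differential abundance analysis of sequence variants with STAMP carries the multiplicity control: p-"values will be adjusted for multiple testing (FDR-adjusted Wald Test"). The section then closes with a general threshold: a p-"value or q-value ≤0.05 will be considered as statistically significant". Neither is linked to the random forest.

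On the data available, the Sample size section says that "a patient cohort of 300 cases is expected within 2 years" and that "30 patients in the conducted cohort are estimated to have unfavorable treatment outcomes".

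**The concern.** A random forest scores each taxon by how much it contributes to the forest's splits or predictions. The scores order the taxa relative to one another. They do not show whether the forest predicts outcome at all. If no taxon is related to outcome, some taxa still come first, and under the stated rule those become the marker taxa.

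An importance rank is neither a p-value nor a q-value, so the closing threshold does not act on it unless someone first attaches a null distribution to the importances. The plan does not say that this will be done. Nor does it say that a top-ranked taxon must also pass the FDR-adjusted abundance test, or that the forest must discriminate better than chance.

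At stake is what the marker result can tell a reader. A screen that always returns names gives no information on whether markers exist. With about 30 events and many more taxa than events, a ranking produced by chance is also hard to tell from a real one by looking at it.

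**Working it through.** **Inputs from the protocol article (Sample size)**
- Cohort: 3 sites × 50 patients per year × 2 years = 300.
- Unfavorable outcomes: 300 × 0.10 = 30.

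Both reproduce the stated figures. The article's only power figure (over 85% for 20% versus 5% dysbiosis, 200 patients and 60 controls) also reproduces. The pooled rate is (40 + 3)/260 = 0.165. The null standard error is √[0.165 × 0.835 × (1/200 + 1/60)] = 0.0547. The alternative standard error is √[0.2 × 0.8/200 + 0.05 × 0.95/60] = 0.0399. Power is Φ[(0.15 − 1.96 × 0.0547)/0.0399] = 85.8%. It concerns patients against controls and does not bear on the marker rule, for which no operating characteristic is given.

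**Step 1, by logic.** Write the rule as: markers = the taxa ranked highest by importance. For any dataset on which a forest can be grown, this set is not empty. So the probability that at least one marker is named when no taxon relates to outcome is 1. No assumption about the number or distribution of taxa is needed.

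**Step 2, by simulation under no association.** There were 40 datasets of 300 patients, with the 30 failures assigned at random. The assumptions were 150 taxa with log-normal, zero-inflated relative abundances, 60 trees, Gini importance and 12 taxa tried per split (about √150).

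| Quantity | Result |
|---|---|
| Datasets in which the rule names markers | 40 of 40 |
| Taxa with positive importance (median) | 147 of 150 |
| Top taxon's importance relative to the mean (median) | 4.4 times |
| Out-of-bag AUC, mean (2.5th to 97.5th percentile) | 0.48 (0.39 to 0.60) |
| Datasets with any taxon at q ≤0.05 (Wilcoxon, Benjamini–Hochberg) | 1 of 40 (2.5%) |

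A second simulation with 200 assumed taxa and 500 trees, again 30 against 270, gave an out-of-bag AUC of 0.49 and the same ratio of 4.4.

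**Step 3, reading the results.**
- The ranking looks structured (a top taxon at 4.4 times the mean) when there is no signal.
- Out-of-bag AUC is about 0.5 and would reveal this if the plan required it to be looked at.
- Chance alone took the AUC to about 0.60 at the upper percentile. A fixed hurdle such as AUC above 0.5 would therefore not be enough, and the comparison has to be with a permutation null.
- An FDR condition would also have worked: it fired in 1 of 40 datasets, against 40 of 40 for the rule as written.

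**The case against.** The strongest reply is that this is one sentence in a journal article. Cross-validation, tuning and permutation settings normally sit in an analysis plan, which is not shown here, and their absence is no fault. That is right about the settings, and the point does not rest on them. It rests on the criterion that the article does state, which is rank. An analysis plan that followed the sentence faithfully would inherit the problem.

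The second reply is that the sentence speaks of taxa that correlate with outcome, and that the same section has an FDR-adjusted analysis and a general 0.05 threshold. Read together, these could mean that a forest candidate must also pass the FDR test. Importances can also be given p-values by permutation, and the threshold would then apply to them. This stands in part: the text does not exclude such a reading, and on it the false naming would largely disappear. But the text does not state it either. The FDR adjustment is attached to the STAMP analysis, and nothing makes it a condition for markers.

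The third reply is that the objective is secondary and exploratory, and that ranking candidates is a legitimate output of a screen. This also stands, and it limits the weight of the point. A ranked list presented as exploratory is acceptable. Calling the top of the list marker taxa without any check is not.

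**Conclusion.** The point holds in a limited form. Followed as written, the rule names marker taxa with probability 1 when no taxon relates to outcome. That figure needs no assumption. The supporting figures (AUC about 0.5, a top taxon at 4.4 times the mean importance) rest on 30 events in 300, 150 to 200 assumed taxa, assumed abundance distributions and 40 datasets per simulation, so they are approximate. If adverse effects also counted as unfavorable outcomes there would be more events, but the ranking would still have a top.

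A reader might infer two stronger things. The first is that the marker objective can never return a null result. The documents do not support this, because the section leaves open that the FDR test or the 0.05 threshold is meant to apply. The defect is that it does not say so. The second is that the markers are intended to direct treatment. The Discussion says only that the study's findings might in future help to tailor treatment, and it does not mention markers there. The objective itself is worded as a search for potential markers.

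This should be corrected before the marker analysis is run. It is of moderate weight and does not touch the primary objective.

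**What to change.** In the Microbiome analysis section, replace the rank-only criterion with a rule that can return nothing:

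1. Name potential marker taxa only if the forest's cross-validated (or out-of-bag) AUC exceeds its label-permutation null at 0.05. Any selection of taxa is done inside the folds.
2. If so, name only those taxa whose importance exceeds its own label-permutation null at FDR q ≤0.05.
3. Otherwise report that no marker was found, and present any ranking as exploratory only.

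By construction, step 1 limits the chance of naming any marker when no taxon relates to outcome to about 5%, against 100% now. The number of permutations must be large enough for step 2. With B permutations the smallest possible p-value is 1/(B + 1). A single marker among 200 taxa needs p ≤ 0.05/200 = 0.00025 under Benjamini–Hochberg, so B must be at least 3,999 (for 150 taxa, 0.05/150 gives 2,999).

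The change costs one or two sentences and some computing time, and needs no new data. The downside is that the study may report fewer markers, or none.
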